## **STUDY AIM 2: PATIENT-CENTERED OUTCOMES**

### **Research Questions**

1. Does thrice-weekly contact improve patient satisfaction with the program?
2. Does thrice-weekly contact improve quality of life?

Satisfaction and quality of life will be assessed using self-reported questionnaires, Patient Satisfaction Questionnaire (PSQ-30) and SF-12 Health Survey. The two instruments will be individually compared across the two intervention arms (once vs. thrice-weekly) and across all three study arms (once-weekly vs. thrice-weekly vs. usual care).

Categorical answers to the questions will be compared using appropriate chi-squared tests (univariate), and logistic or multinomial models (multivariate). Univariate comparisons of quality of life scale (based on SF-12®) (bounded 0 to 1) across the three arms will be assessed using ANOVA and post-hoc pairwise tests with an inverse normal transformation.

Quality of life will be related to participant characteristics (i.e., age, sex, race/ethnicity, anthropometry, nutrition, pharmacotherapy, family history, exercise in the home environment, etc) to assess which patient factors are associated with increased quality of life. Mixed-effects modeling and clustering methods will be employed. Clustering methods, such as hierarchical clustering, will be used to identify clusters of participant that have similar quality of life levels. Then a comparison of the participant characteristics of those identified in the same cluster will be performed to understand patterns in quality of life scores.

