#### **Patient-Centered Outcomes**

1. By the end of Phase 1, study participants who attended thrice-weekly group exercise sessions (Arm 2) should report greater level of satisfaction with the IMPACT exercise program compared to study participants who attended once-weekly group exercise sessions (Arm 1).
2. By the end of Phase 1, study participants who attended thrice-weekly group exercise sessions (Arm 2) should report greater improvement in quality of life compared to study participants who attended once-weekly group exercise sessions (Arm 1).

3. By the end of Phase 2, study participants who maintained thrice-weekly exercise sessions (Arm 2) should report greater improvement in quality of life compared to study participants who maintained once-weekly exercise sessions (Arm 1).

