6. MAQ, FFQ, SF-12, EBBS
7. Review of final eligibility checklist
8. Official participant enrollment
9. Randomization
10. Introduction and instruction distribution

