### **Statistical Analysis**

In univariate analyses, the percent change from baseline will be compared across intervention arms using appropriate parametric (ANOVA, *t* tests) or non-parametric (Wilcoxon) methods.

In multivariate analyses, change in outcomes will be modeled using linear regression. Percent change from baseline will be a continuous outcome with intervention arm as the predictor of interest and various participant characteristics as covariates (e.g. sex, age, race/ethnicity, anthropometry, self-reported diet and exercise, pharmacotherapy, family history, etc.). Repeated measures analysis using the outcome at different time points and mixed-effects models will also be performed. Available nonparticipants will serve as contemporaneous comparators to address possible secular trends in outcome values.

Study participants in the exercise program may also be undergoing concomitant pharmaceutical therapy to reduce HbA1c. The approach is to repeat the above analyses stratified by use of hypoglycemic medication. Another approach is to use a composite binary outcome variable for whether participants were successful in either decreasing diabetes medication or reduced HbA1c by 0.5% without increasing medications. Logistic regression will be used to assess the likelihood of achieving the composite outcome.

Study participants will be studied based on their randomized assignment (intention-to-treat). In sensitivity analyses, participants may be re-analyzed based on actualized attendance if they more closely resemble one of the other arms (once-weekly, thrice-weekly, usual care). A study participant assigned to thrice-weekly, who attends only once a week may be re-analyzed as a weekly patient. Stratification by adherent (attendance >80%) or not will also be another sensitivity analysis.

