Specific Aim 2 seeks to compare the satisfaction of patients between groups as measured by self-reported satisfaction questionnaires. The data will be collected using ordered, multi-point Likert scales, and in some cases responses will be dichotomized (e.g. 5 points with 1-3 vs 4-5). For a power/sample size estimate, we used a difference in proportion estimate. Using a likelihood ratio, chi-squared test of two proportions,  $\alpha = 0.05/3 = 0.016$ , power=0.80 and an underlying referent satisfaction of 80% and equal sample sizes of 92-115/arm per above, we are able to detect minimum differences in proportions of 15 percentage points, and minimum detectable odds ratios 4.9. To compare the quality of life metrics of patients between groups as measured by SF-12,® the data will be collected using SF-12® and appropriately converted to a bounded value between 0 and 1. In analyses, we will use the inverse normal transformation of quality of life to obtain a normally distributed quality of life value. For a power/sample size estimate, we estimated the difference in score, using a two-sample *t* test with pool variance of 0.09, the Delta Method and Taylor Series expansion, properties of the inverse normal transformation,  $\alpha = 0.05/3 = 0.016$ , power=0.80, and equal sample sizes of 92-115/arm per above. We are able to detect a minimum difference in quality of life scores of 0.09 (e.g. 0.50 vs 0.59 would be detectable, on a scale from 0-1).

Cost-effectiveness (Specific Aim 3) analyses use aggregate cost and effectiveness values, along with confidence intervals derived from a bootstrap method. Therefore, sample size meeting the criteria for the above two aims would be sufficient for Specific Aim 3. Missing data will be mitigated through retention strategies (see Section C.8) and augmentation with EHR data (see Section C.5.3). For patients missing some, but not all, follow-up data, the missing data mechanism will be explored and modern imputation methods such as multiple imputations will be used to impute missing covariates following satisfaction of the method's assumptions.

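### The arm comparison of quality of life omits baseline SF-12, although the hypotheses concern improvement, and uses a transformation with no rule for scores of 0 or 1

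*Protocol*

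**What the plan says.** **Hypotheses.** Section 2.3.b (Patient-Centered Outcomes) sets Arm 2 against Arm 1 twice. By the end of Phase 1, thrice-weekly participants "should report greater improvement in quality of life compared to study participants who attended once-weekly group exercise sessions (Arm 1"). By the end of Phase 2, those who kept up three sessions a week "should report greater improvement in quality of life compared to study participants who maintained once-weekly exercise sessions (Arm 1").

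**General approach.** The opening of section 6.2.a speaks of associations with changes in clinical outcomes, patient-centered outcomes and cost.

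**Arm comparison.** Under Study Aim 2 in section 6.2.a, the univariate comparison of the SF-12-based scale "across the three arms will be assessed using ANOVA and post-hoc pairwise tests with an inverse normal transformation". No visit, change score or baseline covariate is named. The modelling that follows is meant "to assess which patient factors are associated with increased quality of life. Mixed-effects modeling and clustering methods will be employed". Its list of participant characteristics does not include baseline SF-12.

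**Power.** Section 6.2.b says the SF-12 will be "appropriately converted to a bounded value between 0 and 1" and that "we will use the inverse normal transformation of quality of life to obtain a normally distributed quality of life value". It uses a pooled variance of 0.09, the Delta Method, alpha 0.016, 80% power and 92 to 115 per arm. It states a detectable difference of 0.09, illustrated as 0.50 against 0.59.

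**Baseline data.** The baseline steps in section 3.2.b include "MAQ, FFQ, SF-12, EBBS". The table in section 4.1.b has SF-12 at all six visits.

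**The concern.** For Aim 1 the protocol says outright that "the percent change from baseline will be compared across intervention arms". For quality of life, the passage that fixes the test and the passage that powers it both describe a comparison of levels, and neither uses the baseline value. An analyst who follows them literally would discard a measurement that every randomised participant has. SF-12 is not a stratification factor (section 6.1.a uses age, gender and HbA1c), so nothing in the design protects against a chance difference between arms in starting quality of life.

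The second concern is the transformation. If it is the pointwise inverse normal function, a score of exactly 0 or 1 has no finite value and the protocol gives no rule for it. Whatever substitute is chosen would then influence the result.

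**Working it through.** **1. The plan's own figure.** Inputs from 6.2.b: variance 0.09 (SD 0.30), alpha 0.016 (two-sided assumed, as sidedness is not stated), power 0.80, n = 92 or 115 per arm.

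Detectable difference = SD × (z for alpha + z for power) × √(2/n), where the two z values sum to 3.251.
- Untransformed scale: 0.30 × 3.251 × √(2/92) = 0.144; with n = 115, 0.129.
- Delta Method at 0.50: SD 0.30/0.3989 = 0.752 on the inverse normal scale, which converts back to 0.141 and 0.126.

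Neither gives the stated 0.09. That is a separate matter and this point does not rest on it. What matters here is that the calculation concerns two follow-up levels and has no baseline term.

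**2. What baseline SF-12 would add.** The protocol gives no baseline-to-follow-up correlation ρ, so a range is assumed. Relative to a comparison of levels, the variance factor is 1 − ρ² with baseline as a covariate and 2(1 − ρ) for a plain change score. Each detectable difference below is 0.144 × √factor (untransformed scale, n = 92 per arm).

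| ρ (assumed) | Variance, baseline as covariate | Detectable difference | Variance, change score | Detectable difference |
|---|---|---|---|---|
| 0.3 | 91% | 0.137 | 140% | 0.170 |
| 0.5 | 75% | 0.125 | 100% | 0.144 |
| 0.6 | 64% | 0.115 | 80% | 0.129 |
| 0.7 | 51% | 0.103 | 60% | 0.111 |
| 0.8 | 36% | 0.086 | 40% | 0.091 |

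The covariate form is never worse than the level comparison. A plain change score gains nothing unless ρ exceeds 0.5.

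**3. The transformation near the ends.** The Delta Method and Taylor expansion in 6.2.b apply to a smooth function of the score, which points to the pointwise inverse normal, Φ⁻¹.
- Φ⁻¹(0) = −∞ and Φ⁻¹(1) = +∞. A mean, SD or ANOVA that includes either value is undefined.
- Substitutes for a score of 1 differ widely: 0.99 gives 2.33, 0.999 gives 3.09 and 0.999999 gives 4.75.
- A move from 0.97 to 0.99 counts 2.326 − 1.881 = 0.446. A move from 0.50 to 0.52 counts 0.050. The ratio is 8.9.
- If 5 of 92 patients scored 1 (assumed), they would contribute 5 × 2.326/92 = 0.126, 0.168 or 0.258 to the arm mean under the three substitutes. The target effect on that scale is Φ⁻¹(0.59) − Φ⁻¹(0.50) = 0.228.
- If 1% of patients scored at an end (assumed), the chance of at least one among 276 (3 × 92) is 1 − 0.99²⁷⁶ = 94%. At 0.1% it is 24%.

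**The case against.** **The general rule already refers to change.** The opening of 6.2.a names changes in patient-centered outcomes, so a reader who infers that the plan ignores change altogether goes too far. This stands. But the specific test under Aim 2 and its power basis do not carry the rule through, and the specific text is what an analyst would follow.

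**A level comparison does address the hypothesis.** One might infer that the test answers the wrong question or is biased. It does not and is not. With equal expected baselines under randomisation, the expected difference at follow-up equals the expected difference in improvement on the same scale. This stands fully and limits the loss to precision and chance imbalance.

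**Covariates are detail for the statistical analysis plan.** In part. However, the protocol positively fixes an unadjusted ANOVA on a transformed scale, and an analysis plan that follows it would inherit both. The mixed-effects sentence does not cure this, since it serves the search for patient factors and not the arm comparison.

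**The infinity is conditional.** This also stands. A scale bounded by 0 and 1 need not attain its bounds, and the conversion is not given. The stated aim of a normally distributed value would also fit a rank-based version, which is finite. The reading that the analysis cannot be run is therefore not supported. Nor does section 2.4.c show that ceiling scores are likely. It excludes only those psychiatric limitations that may interfere with participation, everyone enrolled has type 2 diabetes, and no ceiling rate is given.

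**Conclusion.** The point holds as a loss of efficiency and an unsettled specification in a secondary aim. It does not show an invalid test. Adding baseline SF-12 would cut residual variance to about 75%, 64% or 51% at assumed correlations of 0.5, 0.6 or 0.7. Those factors compare adjusted with unadjusted analysis on one scale; they do not measure the effect of also dropping the transformation.

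The concern about the transformation rests on two conditions: that the pointwise form is meant, which the Delta Method suggests but the Aim 2 text does not say, and that the SF-12 conversion can reach or come close to 0 or 1, which the protocol neither excludes nor handles. If both hold, the substitute chosen for a few boundary scores could shift an arm mean by an amount comparable to the target effect.

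**What to change.** In section 6.2.a, Study Aim 2, replace the ANOVA sentence with a comparison of SF-12 between arms at the 6-month visit (end of Phase 1) and the 30-month visit (end of Phase 2). Use a linear or repeated-measures model with arm, baseline SF-12 and the randomisation strata, on the untransformed score, and report the adjusted mean difference. Add a rank-based analysis as a sensitivity check.

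If a transformation is kept, name it and use a rank-based one that is finite at the bounds. State the SF-12 conversion and whether it can reach 0 or 1.

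Align section 6.2.b: drop or rename the transformation, say on which scale the variance of 0.09 is measured, and restate the detectable difference for the revised model with its assumed correlation.

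The cost is protocol wording and one recalculation. SF-12 is already collected at every visit, so no patients, visits or measurements are added.

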### **STUDY AIM 3: COST EFFECTIVENESS**

#### **Research Questions**

1. What is the most cost-effective frequency of PAD-SMAs based on percentage lowering of HbA1c?
2. What is the most cost-effective frequency of PAD-SMA sessions based on quality of life?

The average cost and outcomes of each intervention arm and the usual care arm will be first assessed. Using each cost and effectiveness measure, cost-effectiveness of the three levels of interventions will be computed in comparison to the usual care group.

Cost-effectiveness will be assessed with two indices: (1) average cost-effectiveness for each intervention and control group, defined as  $(\text{total costs})_A / (\text{average effectiveness})_A$  for group A, and (2) incremental cost-effectiveness ratio (ICER) of groups A vs. B, defined as  $\{(\text{total cost})_A - (\text{total cost})_B\} / \{(\text{effectiveness})_A - (\text{effectiveness})_B\}$ . The ICER indicates the expected incremental cost of each intervention arm over no intervention per unit improvement in effectiveness.

Confidence intervals with bootstrapping standard errors will be used to elicit statistical inferences of each index. The indices using varying costing and effectiveness metrics will be compared. By study design, significant differences across the three intervention arms in patient demographic (age, gender, race/ethnicity), clinical (co-morbidities) or behavioral (i.e. adherence) characteristics are not expected. However, if systematic difference in patient characteristics between intervention and usual care group is detected, alternative models specifically adjusting for selection issues will be employed, such as propensity score matching and selection models. Furthermore, heterogeneous treatment effects with subgroup analysis

based on patient gender, age, and baseline clinical conditions (in BMI, HbA1c levels) will be explicitly examined.

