### **Cost-Effectiveness**

The IMPACT study is to evaluate cost-effectiveness based on clinical outcomes and quality of life. This will involve comparing the average cost and outcomes and determining the incremental cost-effectiveness ratio (ICER) for each study arm (Arm 1 vs Arm 2 vs Arm 3).

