### **Cost-Effectiveness**

1. Based on the percentage of reduced HbA1c levels, the experimental interventions (Arm 1 & Arm 2) should be more cost-effective compared to the non-experimental intervention (Arm 3).
2. Based on the percentage of reduced HbA1c levels, the once-weekly group exercise intervention (Arm 1) should be more cost-effective compared to the thrice-weekly group exercise intervention (Arm 2).
3. Based on quality of life, the once-weekly group exercise intervention (Arm 1) should be more cost-effective compared to the thrice-weekly group exercise intervention (Arm 2).

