## 4.2 STUDY INTERVENTION

### 4.2.a THE IMPACT EXERCISE PROGRAM

The study intervention is an exercise program developed by the IMPACT Study and reviewed by [name], PhD, [name], PhD, and [name], DPT, ACT, OCS. [name] is an expert in exercise physiology and exercise psychology and an Assistant Professor at Brown University. [name] is an expert in physiological science and an Associate Research Professor at UCLA School of Nursing. [name] has extensive expertise in physical therapy and is currently the Manager at the PAMF Physical Therapy Center.

The IMPACT Exercise Program is designed for study participants in Arm 1 and Arm 2 to engage in structured exercise activities in a clinical setting. The structured exercise sessions are led by instructors and conducted in groups. The entire exercise program is 26 weeks or approximately six months in length and will take place during Phase 1 of the study.

Once study participants are assigned to a study arm, they have entered Study Phase 1. Study participants in both Arm 1 and Arm 2 must schedule and undergo an initial exercise evaluation before beginning the exercise program.

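### Aim 3 asks which exercise frequency is more cost-effective, but its analysis text names usual care as comparator and never requires the thrice-weekly versus once-weekly increment that answers the question

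*Protocol*

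**What the plan says.** Protocol section 6.2.a, Study Aim 3, opens with a question about frequency: "What is the most cost-effective frequency of PAD-SMAs based on percentage lowering of HbA1c". A second question asks the same on quality of life. Section 2.3.b (Cost-Effectiveness) makes the contrast direct. Hypothesis 2 (on HbA1c) and hypothesis 3 (on quality of life) both state that "the once-weekly group exercise intervention (Arm 1) should be more cost-effective compared to the thrice-weekly group exercise intervention (Arm 2"). Only hypothesis 1 sets the exercise arms against usual care.

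On method, the Aim 3 text says that "cost-effectiveness of the three levels of interventions will be computed in comparison to the usual care group". It offers two indices. One is "average cost-effectiveness for each intervention and control group". The other is the "incremental cost-effectiveness ratio (ICER) of groups A vs. B", which is then interpreted as follows: "The ICER indicates the expected incremental cost of each intervention arm over no intervention per unit improvement in effectiveness".

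The aim statement in section 2.1.d is wider and speaks of "determining the incremental cost-effectiveness ratio (ICER) for each study arm (Arm 1 vs Arm 2 vs Arm 3"). Section 6.2.b likewise describes the cost-effectiveness comparison as one between the two frequencies as well as with usual care.

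**The concern.** Section 1.1.a gives finding the optimal and feasible frequency of contact as the main purpose of the study. On cost, that decision turns on one quantity: what the two extra weekly sessions cost per additional unit of benefit. A ratio of each arm against usual care averages over all of that arm's sessions, so it does not give this quantity. The average cost-effectiveness ratio of each group does not give it either. An analyst who follows the comparator and the interpretation as written could complete Aim 3 without ever computing the contrast that hypotheses 2 and 3 are about. The choice of frequency would then be read from two ratios that do not determine it.

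**Working it through.** Aim 3 states no cost, ratio or threshold, so there is no figure of the plan's own to reproduce. The check applies the protocol's own ICER formula, (cost A − cost B) / (effect A − effect B), to an illustration.

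**Inputs from the protocol**
- Programme length: "The entire exercise program is 26 weeks or approximately six months in length" (section 4.2.a).
- Sessions per week: one in Arm 1 and three in Arm 2 (section 2.2.a). Assigned sessions are therefore 26 × 1 = 26 and 26 × 3 = 78.
- An HbA1c difference of 0.5 points is the planning value in section 6.2.b.

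**Assumptions**
- Each session costs c, and usual care has no programme cost.
- The Arm 2 effect against usual care (e2) is 0.5 points; the Arm 1 effect (e1) is varied.
- As a variant, each exercise participant also carries a fixed cost of 26c, giving totals of 52c and 104c.

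**Central case, e1 = 0.3 and e2 = 0.5**
- Arm 1 vs usual care: 26c / 0.3 = 87c per point.
- Arm 2 vs usual care: 78c / 0.5 = 156c per point.
- Arm 2 vs Arm 1: (78c − 26c) / (0.5 − 0.3) = 260c per extra point.

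Here the usual-care ratio understates the step by (260 − 156) / 260 = 40%.

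**Consequence for the choice**, using net benefit = value per point × effect − cost:
- At 200c per point, Arm 1 gives 60c − 26c = 34c and Arm 2 gives 100c − 78c = 22c. Arm 2 looks acceptable against usual care (156c is below 200c), yet Arm 1 is the better choice.
- At 300c per point, Arm 1 gives 90c − 26c = 64c and Arm 2 gives 150c − 78c = 72c. Arm 1 has the lower ratio against usual care, yet Arm 2 is the better choice.

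**Direction of the discrepancy.** For e2 > e1, the step costs more than the Arm 2 usual-care ratio when e1/e2 exceeds cost 1/cost 2. That limit is 26/78 = one third (e1 above 0.167) without the fixed cost, and 52/104 = one half (e1 above 0.25) with it.

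| e1 | Fixed cost | Arm 1 vs usual care | Arm 2 vs usual care | Arm 2 vs Arm 1 |
|---|---|---|---|---|
| 0.10 | 0 | 260c | 156c | 130c |
| 0.167 | 0 | 156c | 156c | 156c |
| 0.20 | 0 | 130c | 156c | 173c |
| 0.30 | 0 | 87c | 156c | 260c |
| 0.40 | 0 | 65c | 156c | 520c |
| 0.20 | 26c | 260c | 208c | 173c |
| 0.25 | 26c | 208c | 208c | 208c |
| 0.30 | 26c | 173c | 208c | 260c |

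In the first and sixth rows the usual-care ratio overstates the step. In the second and seventh rows the two agree.

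**The case against.** The strongest reply is that the head-to-head contrast is already there. The ICER is defined for any pair of groups, section 2.1.d names all three arms, and section 6.2.b puts once against thrice weekly. This stands in part. A reader might infer that the plan computes cost-effectiveness only against usual care; the documents do not support that. What remains is an inconsistency: the contrast is permitted and implied, while the sentence on what will be computed and the sentence on what the ICER means both point elsewhere.

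A second reply is that the protocol contains no rule that the frequency with the lower usual-care ratio wins. That is correct. The lowest-ratio reading in the working shows what the stated indices could lead to; it is not a procedure in the plan. It would go too far to say that the design fixes the verdict for once-weekly exercise.

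Third, the illustration rests on assumed costs. Both exercise arms share items such as three exercise evaluations and a resistance band (section 4.2.a), and such shared costs move the break-even point. This also stands. A reader might infer from the central case that the usual-care ratio always understates the price of the extra sessions; the table shows that it need not.

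Fourth, net-benefit methods and dominance checks are commonly left to a statistical analysis plan. That is fair for the detail. The comparator and the interpretation, however, are written in the protocol, and an analysis plan that followed them literally would inherit the mismatch. The count of three levels set against usual care is editorial; the Aim 1 text also counts usual care among three intervention arms.

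**Conclusion.** The point holds as an internal inconsistency with a practical consequence. Hypotheses 2 and 3 and both Aim 3 questions need the Arm 2 versus Arm 1 increment. The Aim 3 analysis text permits it but does not require it, and it interprets the ICER against a different comparator. In the central illustration the gap is 156c versus 260c per point, and the preferred frequency can be misjudged either way depending on the value placed on a point. Neither sign nor size is general. Both depend on costs and on an Arm 1 effect that the protocol does not give, and on taking the 0.5-point planning difference as the Arm 2 effect. The same reasoning applies on the quality-of-life scale, where no figures were worked. The matter is worth correcting because frequency is the study's main question and the correction is small.

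**What to change.** In section 6.2.a, Study Aim 3:
- Keep both comparisons with usual care; hypothesis 1 needs each exercise arm against Arm 3.
- Add the Arm 2 versus Arm 1 incremental cost, incremental effect and ICER, with a bootstrap interval, for HbA1c and for quality of life. Report this contrast even if an ordering of the arms would remove Arm 1 by extended dominance.
- State that hypotheses 2 and 3 are judged on that increment, or on its net benefit over a range of values per unit of effect.
- Amend the interpretation of the ICER so that it covers the between-frequency comparison as well as the comparison with no intervention.
- Replace the count of three intervention levels with the two exercise frequencies.

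The cost is a wording change and one further contrast from data already planned. The downside is a wider interval for the Arm 2 versus Arm 1 contrast. Net benefit helps here, because a ratio becomes unstable when the difference in effect between the two arms is small.

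### Aim 3 puts standard-error intervals on cost-effect ratios whose denominator can be near zero, and its sample-size claim does not follow from using a bootstrap

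*Protocol*

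**What the plan says.** Protocol 6.2.a, Study Aim 3, names two indices. The first is an "average cost-effectiveness for each intervention and control group", a group's total costs over its average effectiveness. The second is an "incremental cost-effectiveness ratio (ICER) of groups A vs. B, defined as" the difference in total cost over the difference in effectiveness. Effectiveness is HbA1c lowering in one research question and quality of life in the other. For inference the section states: "Confidence intervals with bootstrapping standard errors will be used to elicit statistical inferences of each index".

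Protocol 6.2.b speaks more loosely of intervals obtained by a bootstrap method, and concludes from this that "sample size meeting the criteria for the above two aims would be sufficient for Specific Aim 3". The same section counts cost-effectiveness among the primary analyses, although 2.3.b lists its hypotheses as secondary. Two of the three cost hypotheses in 2.3.b set Arm 1 against Arm 2.

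**The concern.** Both indices are ratios. If the denominator has appreciable probability near zero, the ratio has no finite variance. A bootstrap standard error can still be computed, but it is driven by the few resamples whose denominators fall closest to zero. An interval of estimate plus or minus a multiple of that number is unstable.

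Two denominators are exposed:
- The Arm 2 vs Arm 1 HbA1c difference. If Arm 2 beats usual care by the design difference of 0.5 points and Arm 1 lies between them, this contrast is smaller than 0.5.
- The usual-care arm's own HbA1c change, which is the denominator of its average ratio and may be close to zero.

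At stake is whether the Aim 3 intervals can tell the reader anything about the hypotheses in 2.3.b. Separately, the plan asserts an adequate sample size for Aim 3 on a ground that cannot establish it.

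**Working it through.** **Step 1. The plan's own sample size.** Inputs from 6.2.b: 0.5-point difference, 80% power, alpha 0.05/3 (taken as two-sided), baseline mean 6.5%, 92 per arm, 20% attrition. 92/0.80 = 115 and 3 × 115 = 345, as stated. The SD is not stated. With SD 1.0, a two-sample t-test on log HbA1c with effect log(7.0/6.5)/(1.0/6.5) gives 91.7, so 92 is reproducible.

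On the HbA1c scale by normal approximation:

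SD = 0.5 / [(2.394 + 0.842) × √(2/92)] = 0.5 / (3.236 × 0.1474) = 1.048.

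Taking log(7.0/6.5) or log(6.5/6.0) as the effect moves this between 1.01 and 1.09. I use 1.048, assuming it applies to the HbA1c difference analysed in Aim 3.

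**Step 2. The ICER denominator.** SE = 1.048 × √(2/92) = 0.1545 and z = difference/SE. The chance that the 95% interval for the effect difference includes zero is Φ(1.96 − z) − Φ(−1.96 − z). When it does, the ICER has no ordinary bounded interval. The plan states no confidence level for Aim 3; 95% is my choice.

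| True difference (points) | z | Interval includes 0 | Estimated difference ≤ 0 |
|---|---|---|---|
| 0.5 | 3.24 | 10% | 0.06% |
| 0.3 | 1.94 | 51% | 2.6% |
| 0.25 | 1.62 | 63% | 5.3% |
| 0.1 | 0.65 | 90% | 26% |

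Over SD 1.01 to 1.09 the first row runs from 8% to 13% and the third from 61% to 66%.

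**Step 3. Sensitivity to the SD of change.** If 1.048 is the SD of a level and change is analysed, the SD becomes 1.048 × √(2(1 − ρ)), where ρ is the correlation of baseline with follow-up. At ρ = 0.5 it is unchanged. The documents give no ρ.

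| ρ (assumed) | Includes 0 at 0.5 | Includes 0 at 0.25 |
|---|---|---|
| 0.5 | 10% | 63% |
| 0.6 | 5% | 56% |
| 0.7 | 1% | 45% |
| 0.8 | 0.1% | 28% |

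**Step 4. The usual-care average ratio on HbA1c.** SE of one arm's mean change = 1.048/√92 = 0.109. If true mean lowering is 0, the estimate is at or below zero in 50% of trials. At 0.1 points z = 0.92 and the figure is 18%; at 0.2 points z = 1.83 and it is 3%. In those trials the ratio has the wrong or an arbitrary sign.

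**Step 5. What the bootstrap standard error does.** This is illustration only, because the documents give no costs. It assumes gamma costs with means 6,000 and 5,000 per patient, coefficient of variation 0.5, costs drawn independently of effects, 92 per arm, 600 trials and 1,000 resamples each.
- At a true difference of 0.5 (true ICER 1,000/0.5 = 2,000), 48% of trials had at least one resample with an effect difference at or below zero. The standard-error interval had median width 8,137 and 90th percentile 241,143.
- At 0.25 (true ICER 4,000), median width was 279,358. The percentile interval for the ICER had median width 43,297, so it is no remedy either.
- Across differences of 0.5, 0.25 and 0.1 and coefficients of variation of 0.5 and 1.0, the standard-error interval covered the true ICER in 96% to 99% of trials.

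**Step 6. The sufficiency statement.** The Aim 1 and Aim 2 calculations use an HbA1c difference, a satisfaction proportion and a quality-of-life score. No cost variance, cost-effect correlation, precision target or value per unit of effect appears. Resampling estimates uncertainty at a given sample size; it does not make that size adequate.

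**The case against.** Several points against this are sound.

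- **Size.** The SD is back-solved and the costs in Step 5 are invented, so the simulated widths are not facts about this trial. At the design difference most trials would have a bounded interval. A reader might infer that Aim 3 intervals are often meaningless throughout; the figures support that only for smaller differences and for the usual-care ratio on HbA1c.
- **Direction of harm.** A reader might also infer that the Arm 1 vs Arm 2 ranking would be reported backwards. Coverage of 96% to 99% means intervals that are too wide, not falsely confident. The effect difference takes the wrong sign in only 5.3% of trials at 0.25 points.
- **A missing Arm 2 vs Arm 1 comparison.** The sentence that "cost-effectiveness of the three levels of interventions will be computed in comparison to the usual care group" invites that reading, but the ICER is defined for any two groups, and 2.1.d promises "comparing the average cost and outcomes and determining the incremental cost-effectiveness ratio (ICER) for each study arm" across all three arms. This is a tension in wording, not an absent contrast.
- **Units.** Total cost over average effectiveness looks like a scale error. Yet the same section first assesses average cost, and total costs may mean all cost components per patient. With equal arms a literal total is only a scale factor, so this is an ambiguity.
- **Quality of life.** The near-zero argument for usual care does not carry over if effectiveness is a level on a 0 to 1 scale, and none of the figures above covers that measure.
- **Level of detail.** The type of bootstrap interval is often left to an analysis plan, and the wording in 6.2.b would allow others.

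The last point does not rescue the plan: 6.2.a itself fixes standard errors for each index, and Step 5 shows that a percentile interval on the ICER is also very wide at the smaller difference. Nothing in the documents supports the step from bootstrap to sufficiency.

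**Conclusion.** The concern holds on two points.

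First, standard-error intervals for the two ratios are unsound where the effect denominator can approach zero, as it can for Arm 2 vs Arm 1 on HbA1c and for usual care's own HbA1c change. On an SD of 1.048 the ICER lacks an ordinary bounded interval in about 10% of trials at 0.5 points and about 63% at 0.25, and less often if the SD of change is smaller. The likely result is an inconclusive Aim 3.

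Second, the claim that the sample size is sufficient for Aim 3 is unsupported. The documents do not show the sample to be too small either: without cost inputs, neither can be shown. The point matters because 6.2.b places cost-effectiveness among the primary analyses. It should be changed, but it does not touch the HbA1c comparison in Aim 1.

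**What to change.** In 6.2.a, Study Aim 3:
- Replace the standard-error intervals with inference on incremental net benefit. Resample each participant's cost and effect together, give percentile intervals, and show an acceptability curve over a stated range of values per unit of effect.
- Report the ICER with its joint cost-effect uncertainty, on the cost-effectiveness plane or as a Fieller region.
- Drop the average ratio for usual care on HbA1c change.
- As clarifications only, state that costs are means per randomised participant and that the incremental comparison includes Arm 2 vs Arm 1.

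In 6.2.b, delete the sufficiency claim and describe Aim 3 as estimation.

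The cost is a few sentences and modest programming, with no new data or participants. The one real demand is that a range of values per HbA1c point and per quality-of-life unit must be named in advance.
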